### Procedure

The participants will be informed about the study via obstetric practices, gynecologists, or general practitioners, but can also sign up for participation by own registration via a form on the project’s website. Pregnant women, who are visiting their health professional, will be given a brief explanation via a flyer. Women, who are willing to participate, will be asked to scan the QR-code on the flyer and will then be directed to an online registration form where they will fill in the contact details. This information will then be sent to a secured mailbox which can only be accessed by the main researcher. Subsequently, registered participants will be called by the researcher or research assistant who will explain the study in more detail. If participants are willing to participate they will be sent an information letter and consent form, which they will be asked to read, sign and send back. Then, women will be called to screen for exclusion criteria. Eligible women will receive an invitation email with a link to the first online questionnaire (t0). Participants will be assigned an identification number, which will be used throughout the study. To ensure confidentiality, the file including both the participants’ names and identification numbers will be saved with a password that can only be accessed by the principal researcher. After completion of the t0 questionnaire, participants will be randomized. This will be done by sending an email to an independent researcher who has access to the randomization list. The randomization list is created with blocks of 2, 4, and 6 participants, each containing equal numbers of participants allocated to the intervention and active control group, using an online randomization program. The independent researcher will send an email with information about the assigned group. Participants assigned to the intervention group receive an email with a link to download the application on their smartphones. The control group will be sent a link to the website with the psycho-education module, which they can access as frequently as they desire. After 8 weeks, participants will receive an invitation to complete the second questionnaire (t1). Two follow-up questionnaires will be sent, the first at two weeks after birth (t2) and the other at three months after birth (t3). Participants will receive 7.50 euros on their bank account for each completed questionnaire.

#### Intervention

The eHealth intervention “Together with Eva” of the current study consists of an 8 weeks lasting intervention offered on the participant’s smartphone. The intervention consists of an integration of an existing smoking cessation online intervention (www.mijnkoersroken.nl; developed by Trimbos institute) and an HRV-BF prototype application, Time2Breathe [55]. The smoking cessation intervention was adapted and personalized, and the HRV-BF prototype application was further developed by Aan Zee into an application including the actual HRV measurement and feedback Software Development Kit (SDK), developed by Happitech. Participants use the application at their own pace. The application consists of different components (see below), which will be supported by short instruction videos to explain the intended use.

##### Personalized stop-smoking plan

After registration in the app, participants will design a personalized stop-smoking plan in which the participant chooses a specific date on which she wants to quit smoking. Moreover, intrinsic motivation for the intended quitting attempt is enhanced by listing personal advantages of quitting and disadvantages of smoking. These lists will be referred to in the exercises in the app. Participants will also designate a person in their social network, who can be approached for help and support in times of craving. The phone number of this person will be saved in the app. When participants click on the button ‘I would like to call someone’, they will immediately be directed to call this number.

##### Smoking diary

During the 8 weeks of the intervention, participants will receive daily notifications to fill out their diary. In this diary, participants will report if and how many cigarettes they have smoked. This self-report on their smoking behavior will be used to enable positive feedback. For instance, if a woman has been able to refrain from smoking for a day, a week, and so on, she will receive a positive notification such as “Yes, keep it up!”. Participants can navigate through the diary, which gives a clear overview of the quitting process.

##### Personalized stress reduction training

Another element of the intervention is a personalized stress-reduction training. This training consists of two components: (a) HRV-BF, and (b) psycho-education including personalized and evidence-based problem-solving techniques.

##### HRV-bf

The HRV-BF module in the “Together with Eva”-app teaches the participant the technique of slow-paced diaphragmatic breathing through guided breathing exercises. Breathing in synchrony with the baroreflex, also called resonance frequency, results in a substantial increase in HRV [36]. In the first week of the intervention, participants are instructed to exercise slow diaphragmatic breathing, also called ‘belly-breathing’, without using their phones. From the second week of the intervention onwards, breathing exercises are guided by a breath pacer and visual feedback based on continuous HRV measurement developed by Happitech (Heart Rhythm SDK version 1 Happitech). HRV is measured through photo plethysmography (PPG) with use of the camera and flash on the mobile phone. Throughout the 8-week intervention period, the participant’s resonance frequency is assessed four times using a series of breathing exercises at the following fixed paces of 6.5, 6.0, 5.5, 5.0, 4.5 breaths/min, which is in accordance with resonance frequency protocols (e.g. [35]). The pace resulting in the highest frequency power peak in the low frequency (LF) power band (i.e., 0.04–0.15 Hz) relative to the total power, defined as the 0.02–0.5 Hz power band of HR data, is considered resonance frequency and is the advised breathing pace for the participant. During the regular breathing exercises, the participant is guided towards optimal breathing through the color of the breath pacer, which turns dark purple as the LF power peak increases (see Fig. 2). Panel 1 shows the instruction to breathe in; panel 2 instructs to hold the breath for 1 s; panel 3 instructs to breathe out; and panel 4 shows the adjustment of the color, becoming darker purple, when breathing more in synchrony with one’s baroreflex, which is the desired result of the breathing exercise. Breathing exercises are practiced twice a day at a time convenient for the participant. In the first week, breathing exercises last 5 min, whereas from the fourth week onwards, they last 15 min. After performing a breathing exercise, participants are asked about their experience, as indicated by a happy, neutral, or sad smiley, and whether they felt dizzy or nauseous during the exercise. The daily duration of the paced breathing with HRV-BF and the information about one’s experience will become visible in the diary.

**Fig. 2 Fig2:**
[figure not shown]
Screenshots of Instructions for Breathing in the HRV-BF Module of the Application

Participants assigned to the intervention group will receive a phone call from the researcher or research assistant directly after randomization. The researcher will then instruct the participants to fill out the stop plan and will discuss when the participant is planning to use the app and do the breathing exercises. Participants are instructed to start using to app on that same day or the next day. Based on this schedule, researchers will have weekly phone calls with the participants to monitor the planning and, if necessary, adapt it for the following week.

##### Psycho-education on pregnancy, relaxation, and smoking cessation including personalized and evidence-based problem-solving techniques

A psycho-education module, called ‘Lessons’, offers participants written information about pregnancy, stress and relaxation, and smoking and smoking cessation. The lessons about pregnancy provide written information that matches with the gestational age of the unborn (estimated date of birth filled in at registration). In the lessons about stress and relaxation, participants can for instance read about what stress does to the body and mind, tips on stress management and how feelings of tension can be reduced, which is supported by evidence-based problem-solving exercises. With these problem-solving techniques, women can address their own problems or stressful situations, with guidance from the eHealth application. An important first step in this stress reduction is making a stress diary using notes written with pencil and paper, to identify stressful situations and problems. Next, women will be asked to make a clear difference between problems that can be solved and those that cannot be solved, but need to be accepted. Acceptance and tolerance for the unsolvable problems and associated emotions are boosted by building awareness that emotions related to these problems will pass. Then, active problem-solving techniques are built up in subsequent steps to deal with the potentially solvable problems: (1) the identification of a stressful situation or problem that causes stress that may be solvable, (2) the definition of one’s goal and how the problem hampers that goal, (3) finding solutions, also through seeking social support, (4) planning solutions, (5) implementing solutions, (6) taking stock: reviewing one’s situation again and see if there is a continuous need to deal with the problem more actively. In the lessons about smoking cessation, information about the effects of stopping smoking cigarettes on your body and mind is provided, and participants receive tips to refrain from smoking. Also, frequently asked questions about smoking and quitting will be discussed. New lessons will appear every week. If participants do not use the application as intended, they will be reminded by a text message, or a phone call if needed. Contact information of the researcher and of a person independent of the study is mentioned under ‘Contact’ so that the participants will always be able to ask questions if things are unclear or if they need help with exercises. Questions will be answered within 24 h on weekdays.

##### The craving-button and the smoked-button

A craving button ‘Help, I feel the urge to smoke’ is included on the home-screen of the app, which can be pressed when the participants expriences craving. When participants click this button, they will be asked several questions to find out what kind of information or exercise is desired to provide them with distraction and/or support to resist the sense of craving. Participants will either be recommended to talk to someone (i.e. social support that they have designated in their stop plan), to do something relaxing or distracting (e.g. a slow breathing exercise, going outside), or to read something (psycho-education modules). Furthermore, the button ‘Oops, I have smoked’ will help participants to deal with negative thoughts after they have smoked.

#### Control condition

The control condition consists of a website designed specifically for this study consisting of psycho-education on pregnancy, smoking during pregnancy, and stress. The information on the website is a summary of the psycho-education modules on stress, smoking and smoking cessation, and pregnancy included in the app-intervention. Since the website does not include exercises, it is less personalized, less intensive and interactive when compared to the intervention. This webpage can be visited as often as the woman desires and can be accessed on smartphone or computer.

### Outcome measures

At four different time points, women will receive online questionnaires. Each questionnaire will take approximately 15–20 min to complete. The first questionnaire is a baseline questionnaire (t0, before randomization) including the main outcomes and demographic information (i.e. date of birth, weeks of pregnancy, ethnicity, educational level, employment status, relationship status, smoking behavior partner, living conditions). Eight weeks and one day after group assignment, participants will receive the second questionnaire (t1), through which post-intervention measurements will take place. Follow-up questionnaires will be sent two weeks after birth (t2) and three months after birth (t3). In Fig. 1, an overview of the outcome measurements for each time point is depicted. Prior to t1, t2, and t3, a screening question will appear asking about the health of the baby. In case of pregnancy loss or if the baby died after birth, participants will be advised to quit the study participation. They will still receive the agreed compensation for the completed questionnaires.

#### Primary outcome

##### Smoking cessation

Smoking cessation and abstinence will be assessed using a self-report question ‘Do you smoke?’ (yes/no). If answered with ‘yes’, an additional question asking whether she smokes on a daily basis will indicate the frequency of the smoking behaviour.

#### Secondary outcomes

##### Smoking behavior

If participants indicate that they (still) smoke, they will be asked the number of cigarettes smoked per day. Thereby, it can be assessed whether the participant’s smoking behavior changed between the different time points.

##### Birth outcomes

Birth outcomes such as gender, birth date, gestational age and weight at birth will be assessed with self-constructed questions. Moreover, 1- and 5-min Apgar scores will be asked. These scores can be found in a booklet that women usually receive after delivery in the Netherlands. In case these scores are unknown to the women, consent will be asked to contact the midwifery practice in order to obtain these scores.

##### Infant temperament

Infant temperament will be measured at 3 months of age using the short version of the Infant Behavior Questionnaire (IBQ-R; [56]). From the total of 14 scales, the scales ‘Distress to Limitations’ and ‘Fear’, each consisting of 16 items, were used in this study. The mother will be asked to rate the frequency that her baby engaged in specific day-to-day behaviors during the previous week or two weeks on a scale from 1 (never) to 7 (always). Examples for items are ‘After sleeping, how often did the baby cry if someone doesn’t come within a few minutes?’ and ‘When introduced to an unfamiliar adult, how often did the baby refuse to go to the unfamiliar person?’. In a sample of Dutch mothers who reported on the behavior of their 4-month old babies, internal consistency of both the ‘Distress to Limitations’ and ‘Fear’ scale has been found to be good (*α* = .75 and .77, respectively; [57]).

##### Pregnancy-related anxiety

Pregnancy-related anxiety will be assessed using the PRAQ-R2 [58], a short version of the Pregnancy-Related Anxiety Questionnaire (PRAQ; [59]), suited for both women pregnant for the first time, as for women who already have children. The PRAQ-R2 consists of ten items divided into the three subscales (1) Fear of birth (3 items), (2) Worries about Bearing a Physically or Mentally Handicapped Child and complications during and after childbirth (4 items), and (3) Concern about own Appearance (3 items). Examples of items are ‘I am worried about the pain of contractions and the pain during delivery’ and ‘I am worried about the fact that I shall not regain my figure after delivery’, which can be answered on a 5-item Likert scale ranging from 1 (‘Does not apply to me at all’) to 5 (‘Does apply to me a lot’). Higher scores indicate more pregnancy anxiety. Internal consistency of the questionnaire for both nulliparous and parous women is acceptable (Cronbach’s *α* = 0.82–0.85; [58]).

##### Parenting self-efficacy

Parenting self-efficacy will be assessed by the Dutch version of the Maternal Self-efficacy in the Nurturing Role Questionnaire (SENR; [60]) during and after the pregnancy. The SENR has both a prenatal and postnatal version and both versions contain 16 situations regarding (expected, for the prenatal version) feelings of competences in taking care of a child, such as ‘I feel competent in my role as a parent’ and ‘I feel like I am not prepared for parenthood’, answered on a 7-point Likert scale ranging from 1 (Completely disagree) to 7 (Completely agree). A total score will be generated by summing up scores from each item, with higher scores indicating higher parental self-efficacy. Internal reliability has been found to be high (*α* = .86–.89; [61]).

#### Mediator

##### Experienced stress

Experienced stress will be measured using the Dutch, short version of the Perceived Stress Scale (PSS; [62, 63]). This scale consists of 10 items about subjective experiences of unpredictability, lack of control, and burden during the last month, e.g. ‘In the last month, how often have you been angered because of things that were outside of your control?’ Participants indicate on a 4-point scale from ‘never’ to ‘always’ to what extend the items apply to them. Higher scores indicate higher perceived stress. Items and answer categories have been adapted to make it more suitable for our target group. Previous studies reported acceptable to good internal consistency of the PSS (Cronbach’s ﻿α 0.78–0.91; [64]).

#### Moderators

##### User experience

User experience of both the application ‘Together with Eva’ and the webpage (https://www.fgb.vu.nl/nl/onderzoek/stress-en-rookvrij-zwanger) of the control condition will be assessed with several self-constructed questions, such as ‘How many times have you used the app/webpage’, answered by a 5-point Likert scale ranging from 0 (Not much/Never) to 4 (Every day). If they indicate that they have not used the application, they will be asked for the reason. Moreover, attractiveness and ease of use of the application will be assessed with 6 items from the Dutch translation of the User Experience Questionnaire (UEQ; [65]). Participants will answer the question ‘Please indicate what you think about the app’ and ‘Please indicate what you think about the breathing exercises’, answered on a scale from 1 (negative) to 7 (positive), with varying specifications such as ‘not interesting/ interesting’ or ‘unattractive/attractive’. Participants from the intervention group will also be asked if they were motivated to do a breathing exercise when they were stressed and whether they would recommend the application to a pregnant friend who would like to quit smoking.

##### Self-efficacy regarding smoking cessation

Self-efficacy regarding smoking cessation will be assessed by six items from a questionnaire developed by [66]. Participants are asked to indicate whether they are able to refrain from smoking if they find themselves in specific situations, for instance when they feel stressed or tense and when someone offers them a cigarette. Questions can be answered by 0 (never) to 3 (always). Higher scores indicate higher self-efficacy regarding smoking cessation.

##### Perceived mother-child bond

Mother-child bond will be measured using six items derived from a questionnaire developed for Generations^2^ study, which is based on the Treatment Self-Regulation Questionnaire (TSRQ; [67]). This questionnaire has a prenatal version asking about the future mother-child bond, and a postnatal version asking about the current bond of the mother and child. In the first question, the participant will be asked the extent to which she assumes a good relationship with her child is important, which can be answered by five categories ranging from 0 (does not apply to me at all) to 5 (does apply to me a lot). If the participant indicates that the relationship with her child is important to her (answer options 3–5), five items will appear asking about the reason for striving a good relationship. If the participant indicates that relationship with her child is not important (answering options 1–2), she will be asked whether she ever thinks about the relationship with her child. Higher scores indicate a stronger perceived mother-child bond. Internal consistency of the TSRQ was found to be acceptable [67].

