During the last decades, more and more health care is being offered via the Internet, for instance by means of eHealth platforms [39, 40]. Benefits of eHealth are the high accessibility for a large group of people and the usually low cost it entails. Moreover, eHealth is unrestricted by time and place and might reach populations that otherwise do not ask for support, for instance as a result of possible stigmatization. As stigmatization is a common problem among pregnant smoking women [41], and considering the many benefits of eHealth for this group [42], an app-intervention to support pregnant women quit smoking is promising. A recent systematic review supports this, as results show that eHealth approaches were moderately effective on smoking abstinence in a general population of adult smokers [43]. They also emphasize the use of an interactive and tailored approach of smoking cessation interventions.

Considering the benefits of eHealth, we have developed an application including HRV-BF, targeting pregnant women who want to quit smoking. HRV-BF is easy to learn and maintain in daily life, and at the same time requires little efforts. Thus, HRV-BF could be highly appropriate for pregnant smoking women with low SES, who would like to quit smoking. In order to gain knowledge about the underlying mechanisms and conditional factors of treatment effectiveness, various factors that are associated with stress and smoking need to be studied. Factors that may affect the treatment effect obtained in stress reduction and smoking cessation are: pregnancy experience [21], pregnancy-related anxiety [44], self-efficacy regarding smoking cessation [45], a person’s motivation to quit smoking [46], and COVID-19 related stress [47]. Moreover, focusing on indirect treatment effects is also relevant in this transitional and developmental context. For example, factors associated with parenting, such as parenting self-efficacy [48–50] and the bond that the mother feels with her child [51, 52] may also increase when women experience less stress and quit smoking. Parenting factors such as parenting self-efficacy and a warm mother-child bond have been associated with positive effects on child development (e.g. [48, 53]).

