##### Intrinsic motivation

Intrinsic motivation for behavior change will be asked by five questions based on questions from the Treatment Self-Regulation Questionnaire (TSRQ) [69]. Examples of questions are ‘I think that quitting smoking is best for my health’ and ‘I think that quitting smoking is best for the health of my baby’ answered on a five-point Likert scale ranging from (1 = totally disagree, 5 = totally agree). Higher scores indicate higher intrinsic motivation to quit smoking. Internal consistency of the TSRQ was found to be acceptable [69].

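### The items described for perceived mother-child bond ask about the importance of, and reasons for, a good relationship, so they do not support reading a higher score as a stronger bond

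*Protocol article*

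**What the plan says.** The Introduction names the construct of interest as "the bond that the mother feels with her child". It expects this bond may improve when women have less stress and stop smoking, and it links a warm bond to favourable child development. The current study section lists feelings of bonding among the secondary outcomes. The Statistical analyses section assigns bonding a linear mixed model as a secondary outcome and also lists it as a moderator.

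The instrument is set out under Perceived mother-child bond:

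- "Mother-child bond will be measured using six items derived from a questionnaire" developed for another study, "which is based on the Treatment Self-Regulation Questionnaire (TSRQ; [67").
- There is a prenatal version, said to concern the future bond, and a postnatal version, said to concern the current one.
- "In the first question, the participant will be asked the extent to which she assumes a good relationship with her child is important".
- For women who answer in the upper range, "five items will appear asking about the reason for striving a good relationship".
- A woman who answers in the lower range does not get those five items; instead "she will be asked whether she ever thinks about the relationship with her child".
- The reading of the score is fixed: "Higher scores indicate a stronger perceived mother-child bond".
- The only psychometric statement is that the internal consistency of the TSRQ was acceptable.

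**The concern.** The construct and the described items do not match. How much a mother values a good relationship, and why she strives for one, are motivational matters. How close or warm she feels toward the child is a different question. A woman whose present bond is poor could still rate a good relationship as very important and give strong reasons for wanting one.

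If the plan is followed as written, a difference between arms on this score would be reported as an effect of the app on mother-child bonding. An interaction would be reported as bonding changing the treatment effect. Because the Introduction ties bonding to child development, a reader would probably take such a result as a benefit for the child. The items described give no basis for that step.

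**Working it through.** The article gives no numerical result to reproduce here. The check is an item count, followed by a comparison of sections.

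**1. Item count (Perceived mother-child bond).**
- Stated total: 6 items.
- Described for women who rate the relationship important: 1 on importance + 5 on reasons = 6. The description therefore accounts for every item.
- Described for women who do not: 1 on importance + 1 on whether she ever thinks about the relationship = 2.
- Items on either route described as asking about the strength, warmth or quality of the bond: 0.

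**2. Target against content.** The Introduction and The current study speak of a bond that is felt. The same instrument section says in general terms that the two versions ask about the future or current bond. The item-by-item description that follows is more specific and lists only importance, reasons and, on the alternative route, whether she thinks about the relationship. The general phrase is not borne out by the detail.

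**3. Evidence cited.** Internal consistency shows that items hang together, not what they measure. It is also quoted for the TSRQ, which is the parent of the source questionnaire, and not for the six items used. By contrast, the sections on pregnancy-related anxiety and pregnancy experience quote reliability for the scale actually administered. The closing paragraph under Birth characteristics adds that the answer categories of the bond measure were among those reduced or adapted, a further step away from the parent instrument.

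**4. Where the reading is used (Statistical analyses).**
- Secondary outcomes listed for linear mixed models: smoking behaviour, perceived stress, birth outcomes, negative affectivity, self-efficacy, bonding, intrinsic motivation, parenting self-efficacy, pregnancy-related anxiety = 9. Bonding is 1 of 9.
- Moderators listed: program usage and experience, quit self-efficacy, bonding, intrinsic motivation, pregnancy experience = 5. Bonding is 1 of 5, and each is to be tested on 3 outcomes (cessation, smoking behaviour, perceived stress).
- Planned results that carry the bonding label: 1 outcome model + 3 moderation tests = 4.

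**The case against.** The strongest reply is that the item wording is not shown. The article summarises five items in one clause, the source questionnaire is not available, and an article condenses its instruments. The section also says that the two versions ask about the bond, and its label is perceived bond. On this view the scale may be sound and only its summary poor.

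Part of that stands. A reader might infer that the score measures motivation and can never support a conclusion about bonding. The documents do not go that far, because neither the wording nor any validation work on the source questionnaire is shown. No scoring rule is given either, so five of six items is a count and not a weight. It cannot be shown how high a woman with a poor bond would actually score.

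Two further inferences also fail:

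- A reader might conclude that the bond items are taken directly from the questionnaire used for quit motivation. The intrinsic-motivation section says that construct "will be asked by five questions based on questions from the Treatment Self-Regulation Questionnaire (TSRQ"), but under a different reference, and the bond items reach the TSRQ only through an intermediate questionnaire.
- A reader might then say that the two moderators are one construct. They have different objects: the quit-motivation examples concern the health benefit of stopping smoking, while the bond items concern the relationship with the child. A shared ancestor does not make them indistinct.

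What the reply does not remove is that the article itself commits to an interpretation, and its own account of all six items does not support it. This is something stated, not something left to a fuller document.

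**Conclusion.** The concern holds in this form: as described, the six items cover the importance of a good relationship (1) and the reasons for striving for one (5), and this content does not support reading a higher score as a stronger bond. A result on this score should not be reported as an effect on, or moderation by, felt bonding.

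The reach is limited to one of nine secondary outcomes and one of five moderators. The Abstract does not name bonding among its secondary outcomes, and the primary outcome, sample size and primary model are unaffected. It still deserves correction, because the unsupported conclusion is written into the plan and is cheap to prevent.

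The verdict assumes that the article's description of the items is accurate. Evidence that the source questionnaire measures bonding would answer it.

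**What to change.** In The current study, Perceived mother-child bond and Statistical analyses:

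- Label the variable by its described content, for example importance of and motivation for a good mother-child relationship.
- Remove or qualify the sentence that equates a higher score with a stronger bond.
- State that no conclusion about bonding will be drawn from this score unless evidence is cited that the source questionnaire measures bonding. If such evidence exists, citing it would allow the present label to stay.

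The change is to wording only, with no new data and no change to the models. The price is that one secondary bonding conclusion is given up or qualified.

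Adding a new felt-bond question now is not advised. Data collection is already under way, so it would have no baseline value for women already enrolled, would cover only part of the sample, and would itself lack validation.
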